### 2.5. Data Collection Procedure and Statistical Analysis

Once the study subjects have been informed, data will be collected for statistical analysis. The procedure to register different outcomes will be performed at baseline T.0 (Pre), at 4 weeks after the start of the intervention T.1 (Post1), and 8 weeks when the intervention ends T.2 (Post). Schedule of enrollment, interventions, and assessments is shown in Table 1. Initial evaluation (Pre) and measures at four and eight weeks (Post 1 and Post 2) will be carried out by an evaluator at the headquarters designated for this purpose, facilitating the access of the patient and after confirmation of the appointment by the research secretary or by means of telecommunication tools that allow the realization of the different measuring instruments.

The data will be added to the database created for this purpose and managed by the principal researcher using exportable data tables for statistical analysis. Each of the participating subjects will be assigned a study participation number, and the results of each of the variables analyzed will be collected. The principal investigator will be in charge of the anonymization of the data, so that the data will be recorded by eliminating the link with the identifiable person.

#### Statistical Analysis

The results of the research will be presented as a summary of the outcome measures, together with the estimated effect size and its precision. The statistical analysis will be performed according to the intention-to-treat principle using SPSS software.

The filiation data of the participating subjects will be presented by means of frequency tables and histograms. A descriptive statistical analysis of the different variables will be carried out with frequency tables, bars and sectors in order to have as much information as possible for exploration and analysis. The homogeneity of the sample will be analyzed and normality tests will be performed.

The results are evaluated by comparing the differences between the groups with mixed linear model and T-test statistics to test the hypothesis that the means of two groups are or are not significantly different from each other.

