### 2.1. Patients

The study includes adults diagnosed with COVID-19 with mild-moderate and severe-critical respiratory processes who have been treated in hospitals in (south of Spain) and who have been discharged from hospital. The fundamental ethical precepts according to the Helsinki Declaration [35] and Law 14/2007 of 3 July on Biomedical Research will be respected, guaranteeing the protection and confidentiality of data. This trial has the approval of the Andalucía Ethics Committee with HIP version 281020. Patients in the study are required to read and approve the consent form.

Patients must reside or stay in the Andalucía (south of Spain) during the intervention phase, have computer technology with an Internet connection at home (including one of the following devices: desktop personal computer, laptop, tablet or smartphone), and be able to access e-mail or WhatsApp frequently and reliably. Patients who are not in full cognitive capacity to use new technology tools will be excluded.

For the development of this research, an intentional non-probabilistic type of sampling will be used for the convenience of the study, due to the characteristics of the subjects.

A sample size of (*n* = 237) with a proportional distribution for each arm of the study (group TR = 118 + control group = 117) with an expected proportion of losses (R = 15%) and a confidence index IC = 95% was used.

Patients are recruited from hospitals rehabilitation and physiotherapy departments. Strategies to achieve an adequate inclusion of participants that reach the target size of the sample include the multidisciplinary collaboration of south of Spain hospitals, heads of rehabilitation services and Physiotherapist teams. The collaborators will be informed about the characteristics of the study in personal interviews and presentation of the project. Patient recruitment seeks to ensure socio-demographic diversity in relation to social origin, gender, ethnicity and education adapted to the particularities of the reference population in Andalucía and prior information on compliance with data protection laws. We will try to make sure that the sample data are homogeneous at the beginning of the study, trying not to have significant differences in demographic, medical and other variables.

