### 2.2. Randomization and Single Blinding

Before patient inclusion, a research secretary will generate the allocation sequence and randomly assign patients consecutively with opaque sealed numbered envelopes. A computerized random number generator will be used. The research secretary will be instructed not to reveal the allocation sequence to any of the research team. The nature of the intervention in both groups does not allow blinding of patients and physiotherapists. It is therefore a single-blind study, where the evaluator does not know the nature of the intervention.

Study subjects are randomly assigned to either the TR group or the control group through a computerized randomization system. Subjects receive an initial evaluation based on clinical parameters and follow-up discharge reports. Data will be collected by an evaluator and integrated into research databases.

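### A mixed model and a t-test are both named for one between-group hypothesis with no rule on which decides, and the t-test is less precise than a baseline-adjusted model

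*Protocol article*

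**What the plan says.** The Statistical Analysis section of the protocol article evaluates the results by "comparing the differences between the groups with mixed linear model and T-test statistics", in order "to test the hypothesis that the means of two groups are or are not significantly different from each other". Neither method is called primary, supportive or a sensitivity analysis. The section does not say whether the t-test compares final scores or changes, and it lists no covariates for the mixed model. It also states: "The statistical analysis will be performed according to the intention-to-treat principle using SPSS software".

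Section 2.5 and Table 1 schedule the sit-to-stand test, SPPB, SF-12 and EQ-5D at baseline (T.0), 4 weeks (T.1) and 8 weeks (T.2). Section 2.1 allows for 15% losses.

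On baseline balance, section 2.1 states: "We will try to make sure that the sample data are homogeneous at the beginning of the study, trying not to have significant differences". The Statistical Analysis section adds: "The homogeneity of the sample will be analyzed and normality tests will be performed". The population is "adults diagnosed with COVID-19 with mild-moderate and severe-critical respiratory processes".

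**The concern.** Two tests of one hypothesis can give different answers. When nothing says which counts, a positive result from either can be presented as the trial's result, and the nominal 5% error rate no longer describes the procedure.

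The two methods also differ in quality for this design. A t-test on the 8-week score makes no use of the baseline score, and a t-test on change uses it inefficiently. Unless missing values are imputed, a t-test at a visit rests on the patients seen at that visit. A likelihood-based mixed model also uses patients with partial follow-up, under a missing-at-random assumption. With 15% losses expected, the two results could therefore rest on different sets of patients.

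The balance aim in section 2.1 is a smaller point. After randomisation any baseline difference is due to chance, so whether it reaches significance says nothing useful about how to analyse the outcome.

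**Working it through.** **The plan's own figure.** Section 2.1 gives n = 237 and arms of 118 and 117, which add to 235. It states no effect size, SD, margin or power, so the figure can be neither confirmed nor refuted. For this check only the evaluable number matters: 0.85 × 235 = 199.75 and 0.85 × 237 = 201.45, or about 100 per arm.

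**Assumptions.** The document gives no correlation r between baseline and outcome, so r = 0.3 to 0.8 is used. The SD is taken as equal at baseline and follow-up. The 80% power used as a reference point in step 2 is also an assumption.

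**Step 1: variance of the arm difference**, with n per arm and SD σ:

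- t-test on the final score: 2σ²/n
- t-test on change: 2σ² × 2(1 − r)/n
- baseline-adjusted model: 2σ²(1 − r²)/n

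The adjusted variance divided by the final-score variance is 1 − r². Divided by the change-score variance it is (1 − r²)/(2(1 − r)) = (1 + r)/2. Neither ratio exceeds 1 for any r from 0 to 1.

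**Step 2: power.** With 100 per arm and a two-sided 5% level, the standardised difference that gives a final-score t-test 80% power is (1.960 + 0.842) × √(2/100) = 0.396. The power for that same difference after adjustment uses the SD multiplied by √(1 − r²).

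**Step 3: error rate if either test may be declared.** The simulation had no true difference, normal data, complete follow-up, 100 per arm and 20,000 replicates. It compared a final-score t-test with a baseline-adjusted analysis of covariance, which stands in for an adjusted mixed model. Each test alone rejected in 4.8% to 5.3% of replicates.

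| Assumed r | Variance vs final-score t-test | Variance vs change-score t-test | Power after adjustment (final-score t-test: 80%) | Type I error, either test |
|---|---|---|---|---|
| 0.3 | 0.91 | 0.65 | 84% | 6.2% |
| 0.5 | 0.75 | 0.75 | 90% | 7.5% |
| 0.7 | 0.51 | 0.85 | 97.5% | 8.2% |
| 0.8 | 0.36 | 0.90 | 99.7% | 8.5% |

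The simulation error on the last column is about 0.2 percentage points, from √(0.08 × 0.92/20,000) = 0.0019. For comparison, two independent tests would give 1 − 0.95² = 9.75%. The inflation grows with r because the two tests agree less as baseline explains more of the outcome.

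**The case against.** The strongest reply is that the plan already names a mixed model over three visits. That model may well use baseline, and a condensed article need not list covariates. This stands: the precision figures apply against the t-test only, and the gain over the planned mixed model may be nil. It does not answer why an unranked t-test is named beside that model.

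It can also be said that the sentence is compressed and covers every outcome. Costs, for example, have no baseline value, and a t-test would suit them. That is a possible reading, but the text does not assign methods to outcomes and gives one hypothesis for both.

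Several stronger readings are tempting and are not supported:

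- *The t-test contradicts intention-to-treat and would discard about 35 patients (15% of 235).* This depends on how missing values are handled, which the article does not give. The 15% is a sample-size allowance and not a planned exclusion. A repeated-measures model with baseline as covariate likewise gains no outcome information from a patient with no visit after baseline.
- *Baseline balance is checked by significance tests.* The article says homogeneity is analysed; the only tests named in that sentence are for normality. The wording in section 2.1 points towards significance but does not settle it.
- *Recruitment will be steered towards balance and so undermine allocation.* Section 2.1 describes no mechanism. Section 2.2 has the sequence generated before inclusion, kept in opaque sealed envelopes and withheld from the research team.
- *Missing strata, blocks, or centre and severity terms are errors.* They are silence in a condensed article, and the gain from such terms cannot be computed from it.
- *Chance imbalance biases the unadjusted comparison.* Under randomisation it does not; the confidence interval already allows for it. Adjustment improves precision.

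**Conclusion.** The point holds in a limited form. The article fixes two methods for one hypothesis and does not say which decides. If either may be declared, the two-sided type I error is about 6% to 8.5% for r between 0.3 and 0.8, given the simulation's assumptions of normal and complete data and a t-test on the final score.

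The t-test is the less precise choice beside a baseline-adjusted model. The reduction in variance is 9%, 25% and 49% against a final-score t-test at r = 0.3, 0.5 and 0.7, and 35%, 25% and 15% against a change-score t-test. The advantage with partial follow-up is real but conditional: it needs no imputation for the t-test and data missing at random for the mixed model.

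The wording on baseline differences should be corrected, but it is not evidence that allocation is compromised. Choosing one model also leaves a separate matter open. The introduction states a non-inferiority hypothesis without a margin, and a test of difference does not address it.

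**What to change.** - For each outcome measured at T.0, T.1 and T.2, name one confirmatory analysis: a mixed model for repeated measures with baseline score, arm, visit and arm by visit. Report the arm contrast at T.2 with its 95% confidence interval.
- Drop the t-test for these outcomes, or label it supportive with no part in the conclusion. Say separately which method applies to outcomes without a baseline value.
- Add severity class as a covariate if it is recorded at baseline. This is a recommendation and does not correct an error.
- In section 2.1, replace the aim of "trying not to have significant differences in demographic, medical and other variables" with a descriptive baseline table by arm.

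The cost is a few changes of wording in the analysis text. Allocation, visits and data collection are unaffected, so the changes can be made after recruitment has begun, provided they are fixed before outcome data are compared by arm.

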## Abstract

COVID-19 can cause important sequels in the respiratory system and frequently presents loss of strength, dyspnea, polyneuropathies and multi-organic affectation. Physiotherapy interventions acquire a fundamental role in the recovery of the functions and the quality of life. Regarding the recovery phases after hospital discharge, the current evidence available is very preliminary. Telerehabilitation is presented as a promising complementary treatment method to standard physiotherapy. The main objective of this research is to evaluate the effectiveness of a personalized telerehabilitation intervention after discharge from hospital for the improvement of functional capacity and quality of life compared to a program of health education and/or care in a rehabilitation center. As secondary objectives, to identify the satisfaction and perception of patients with the telerehabilitation intervention and the presence of barriers to its implementation, as well as to evaluate the cost-effectiveness from the perspective of the health system. This study protocol will be carried out through a single blind multicenter randomized clinical trial in the south of Spain. We hypothesize that the implementation of a telerehabilitation program presents results not inferior to those obtained with the current standard intervention. If the hypothesis is confirmed, it would be an opportunity to define new policies and interventions to address this disease and its consequences. Trial registration NCT04742946.

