The main objective of this research is to evaluate the effectiveness of a personalized telerehabilitation intervention in patients diagnosed with COVID-19 after discharge from hospital for the improvement of functional capacity and quality of life compared to a program of health education and/or care in a rehabilitation center. As secondary objectives, to identify the satisfaction and perception of patients with the telerehabilitation intervention and the presence of barriers to its implementation, as well as to evaluate the cost-effectiveness from the perspective of the health system. The hypothesis of this research is that the implementation of a telerehabilitation (TR) program in patients with COVID-19 presents no inferior results in the improvement of functional capacity and quality of life compared to those obtained with a health education program and/or care in a rehabilitation center.

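### The hypothesis is non-inferiority, but the stated test is of a difference in means, so a non-significant result could not support it

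*Protocol article*

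**What the plan says.** The hypothesis appears twice in the protocol article. The Abstract says that telerehabilitation "presents results not inferior to those obtained with the current standard intervention". The closing paragraph of section 1.2 says that it "presents no inferior results in the improvement of functional capacity and quality of life" relative to health education and/or care in a rehabilitation centre. The main objective, in the same paragraph, is more neutral: "The main objective of this research is to evaluate the effectiveness of a personalized telerehabilitation intervention in patients diagnosed with COVID-19", compared with control. It names neither superiority nor non-inferiority.

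The Statistical Analysis part of section 2.5 compares the groups with a mixed linear model and with "T-test statistics to test the hypothesis that the means of two groups are or are not significantly different from each other". Results are to be presented "together with the estimated effect size and its precision". On the analysis set it says: "The statistical analysis will be performed according to the intention-to-treat principle using SPSS software".

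Section 2.1 gives a total of 237, arms of 118 and 117, 15% expected losses and 95% confidence. The article states no margin, SD, effect size or power.

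**The concern.** A non-inferiority claim has to reject the null that telerehabilitation is worse by at least a margin. The stated test addresses a different null, that the two means are equal. Failing to reject equality says only that the data did not separate the arms. It does not bound how much worse telerehabilitation might be.

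This is a conflict between two things the article does state, not a detail left to a fuller document. A separate analysis plan with a margin-based rule would have to replace the stated test, not just complete it.

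The article expects confirmation of the hypothesis to inform new policies, and it foresees clinical guidelines on telerehabilitation. A claim of non-inferiority resting on a null result could carry a materially worse programme into practice.

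**Working it through.** **What each result of the stated test can show.** Let D = mean(telerehabilitation) − mean(control), with higher values better, and let M > 0 be a margin.

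- Stated test: H0: D = 0 against H1: D ≠ 0.
- Stated hypothesis: reject H0: D ≤ −M in favour of D > −M.
- Significant, favouring telerehabilitation: the lower 95% limit is above 0, hence above −M for every M. The hypothesis is supported.
- Significant, favouring control: this is evidence of a deficit, and without M its importance cannot be judged.
- Not significant: the interval contains 0, but its lower limit may lie on either side of −M. With no M, nothing follows about the hypothesis.

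**Inputs for the size of the error.** Section 2.1 gives arms of 118 and 117, which sum to 235 (the stated total is 237; I use the arm figures). With 15% losses, 118 × 0.85 = 100.3 and 117 × 0.85 = 99.45, so about 100 and 99 evaluable. The plan has no power or margin figure to reproduce. I therefore assume a true deficit of 0.40 SD, a two-sided 5% level and a plain two-sample t-test. A mixed model would give a somewhat different standard error.

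**Chance of a non-significant result at a true deficit of 0.40 SD.** In SD units, SE = √(1/n₁ + 1/n₂), non-centrality λ = 0.40/SE, and P = P(|T| < t₀.₉₇₅) for a non-central t with n₁ + n₂ − 2 degrees of freedom.

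| Analysed | SE (SD) | λ | Critical t | P(not significant) |
|---|---|---|---|---|
| 100 and 99 | 0.1418 | 2.821 | 1.972 | 0.198 |
| 118 and 117 | 0.1305 | 3.066 | 1.970 | 0.137 |

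The error therefore depends on how many patients are analysed, and it rises as patients are lost.

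**The same deficit under a margin rule.** With M = 0.40 SD, and non-inferiority concluded only if the lower two-sided 95% limit exceeds −M, a true deficit exactly at the margin passes with probability 0.025 at either sample size.

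The like-for-like contrast is thus 0.198 or 0.137 against 0.025.

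**The case against.** **The article never says that a non-significant p-value will be taken as non-inferiority.** A reader might infer this, because the wording treats non-significance as one of two outcomes of the test. The inference is not supported by any statement, so the error rates above are conditional on such a reading. The mismatch between hypothesis and test does not depend on it.

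**The trial can still support its hypothesis.** It would be too strong to say that the plan cannot do so. A significant result favouring telerehabilitation would establish non-inferiority at any margin. That outcome is possible, since section 2.3 allows some controls to receive only home-based health education. The main objective's wording also fits a difference test. What stands is that a non-significant result cannot support the hypothesis.

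**Effect size and precision will be reported, and a margin may exist elsewhere.** This is a fair point. The ingredients of a margin comparison would be available, and I do not treat the missing margin as a separate defect. But the article does state which hypothesis will be tested, and it is not non-inferiority.

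**Smaller deficits give more striking figures.** At 0.2 or 0.3 SD a non-significant result is more likely than at 0.40 SD. Those deficits would lie inside a 0.40 SD margin, so passing them would not be an error by that standard. Only the contrast at the margin is used.

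**Intention-to-treat is the only analysis set named.** Poor adherence can pull arms together and favour a non-inferiority claim, but this is possible rather than certain, and further analysis sets are commonly left to an analysis plan. The point is secondary.

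**Conclusion.** The concern holds in this form: the stated test answers a different question from the stated hypothesis, and only a significant result in favour of telerehabilitation could support that hypothesis as the plan is written. If a non-significant result were nevertheless read as non-inferiority, the chance of that reading at a true deficit of 0.40 SD would be about 20% with 100 and 99 evaluable patients and about 14% with all 235, against 2.5% under a rule with its margin there.

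These figures rest on an assumed deficit, equal SDs, a simple t-test and the 15% loss rate in section 2.1. The value 0.40 SD is illustrative and is not a recommended margin. The mismatch itself rests on no assumption; it follows from the article's own wording.

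**What to change.** Replace the difference test in the Statistical Analysis section with a non-inferiority rule:

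- Name one primary outcome at T.2 (8 weeks), for example the 1-min sit-to-stand test. Fix a clinically justified margin on its own scale. Do this before anyone sees outcome data by arm; patients and physiotherapists are not blinded, so a promise tied to unblinding would protect little.
- Conclude non-inferiority only if the lower limit of the two-sided 95% confidence interval for telerehabilitation minus control, from the mixed model already planned, lies above minus the margin. Test superiority only after that.
- Either set a margin for a named quality-of-life measure as well, or restrict the non-inferiority claim to the named outcome.
- State that a non-significant difference is not evidence of non-inferiority.
- Do not derive the margin from the sample size. State the power that the planned size gives for the chosen margin. For orientation, with about 100 evaluable per arm, no true difference and one-sided 2.5%, power is about 29% for a margin of 0.20 SD, 56% for 0.30 SD, 81% for 0.40 SD and 94% for 0.50 SD (normal approximation; assumed range).
- Add a per-protocol analysis as a supporting check.

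The cost is mainly wording in the protocol and analysis plan, the work of justifying a margin, and one supporting analysis. The downside is that a finding of no significant difference may no longer support the claim, and power for a justified margin may be modest. A margin of 0.30 SD at 80% power, for instance, would need 350 evaluable patients, or 350/0.85 ≈ 412 enrolled.
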